### 2.8. Data Analysis

#### 2.8.1. Statistical Analysis

Descriptive statistics will be estimated for baseline patients and their characteristics. The similarity between groups at baseline will be calculated, followed by examining differences between groups in body weight. Covariates will be screened in bivariate analyses and included in multivariable analysis when related to outcomes *p* < 0.2. Covariates will include age, sex, center, BMI, HbA1c, lipid profile and blood pressure. Adjustment for confounding factors will be examined using linear regression. Questionnaire scores will be assessed, and changes will be sought between baseline, 1 and 6 months and between groups. All statistical analyses will be performed using IBM SPSS statistics version 27.0.

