### 2.3. Sample Size

The primary outcome was body weight change at 1 and 6 months. The power calculation assumed a 14 kg SD in baseline weight and a 0.9 correlation between baseline and 6-month weight [31]. As such, a sample size of 74 (37 per group) was required to give the trial 80% power to detect a 4 kg difference in mean weight change between groups at 6 months (*p* < 0.05, two-sided test).

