### 2.7. Outcomes of Interest

#### 2.7.1. Primary Outcome

The primary outcome will be identifying changes in body weight from baseline to 1 and 6 months and between groups. To measure body weight and BMI, we will use TANITA MC-780MAS Segmental. In the welcome session, participants will be presented with the primary outcome, which is maintaining a healthy weight or losing 5% if overweight.

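### The 37 per group is the figure for an analysis adjusted for baseline weight, but the analysis section omits baseline weight and picks covariates by a p<0.2 screen; the power cost is modest and the primary model should be fixed in advance.

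*Protocol article*

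**What the plan says.** Section 2.3 gives the sizing assumptions: "The power calculation assumed a 14 kg SD in baseline weight and a 0.9 correlation between baseline and 6-month weight". The target is "80% power to detect a 4 kg difference in mean weight change between groups at 6 months", with a two-sided 5% test, and the result is 37 per group, 74 in all. The section does not name the model behind the calculation.

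Section 2.7.1 defines the outcome as change: "The primary outcome will be identifying changes in body weight from baseline to 1 and 6 months and between groups". The abstract and section 2.3 do the same.

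Section 2.8.1 describes the analysis. It plans a check of baseline similarity, then a look at group differences in body weight, without saying whether the response is change or weight at follow-up. Adjustment follows by linear regression. The selection rule is "Covariates will be screened in bivariate analyses and included in multivariable analysis when related to outcomes" at p<0.2, and the candidates are listed: "Covariates will include age, sex, center, BMI, HbA1c, lipid profile and blood pressure". Baseline weight is not among them, and no other section says that the primary model conditions on it.

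**The concern.** Two stated parts of the protocol do not fit together. The sample size uses the correlation between baseline and 6-month weight in the way a baseline-adjusted model does. The analysis section lists its covariates and leaves out the one variable that gives this precision.

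The selection rule is a problem in its own right. In a randomised trial, adjustment serves mainly to gain precision, and the useful covariates can be named before any data are seen. A screen against the outcome settles the model only once outcomes are known, and may settle it differently at 1 and 6 months. It also ignores group. The outcome contains the treatment effect, so a covariate that happens to be imbalanced between groups is more likely to pass and then to absorb part of that effect. What is at stake is some power and a primary estimate that depends on which covariates passed.

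**Working it through.** **Inputs (section 2.3).** SD 14 kg; baseline to 6-month correlation r = 0.9; difference 4 kg; two-sided 5%; 80% power; 1:1 allocation (section 2.1). The SD is assumed equal at both times. No dropout allowance is used.

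**Formula.** n per group = 2*(1.960+0.842)^2*SD^2/4^2. With unrounded quantiles the squared sum is 7.849.

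**Reproducing the protocol's figure: adjusted for baseline weight.**
- SD = 14*sqrt(1-0.9^2) = 6.10 kg
- n = 2*7.849*37.24/16 = 36.5, so 37 per group, which matches.

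**Unadjusted change score.**
- SD = 14*sqrt(2*(1-0.9)) = 6.26 kg
- n = 2*7.849*39.2/16 = 38.5, so 39 per group (78 in all).

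**Unadjusted 6-month weight.**
- SD = 14 kg
- n = 2*7.849*196/16 = 192.3, so 193 per group.

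**Power at 37 per group.**

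| Analysis | Normal approximation | Noncentral t |
|---|---|---|
| Adjusted for baseline weight | 80.5% | 79.4% |
| Unadjusted change | 78.5% | 77.4% |
| Unadjusted 6-month weight | 23.2% | 22.8% |

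**Would the listed covariates stand in for baseline weight?** BMI could, in part. Suppose BMI is always in the model and acts only through weight, with an assumed BMI-weight correlation of 0.5 to 0.9. Power for change is then 79.0% to 80.1% (normal approximation). But the stated rule does not force BMI in. Under the protocol's inputs the correlation of change with baseline weight is -(1-0.9)/sqrt(2*(1-0.9)) = -0.22. At N = 74, a p<0.2 screen on change would admit BMI about 61% to 68% of the time (assumed BMI-weight correlation 0.8 to 0.9). It would admit baseline weight itself, if listed, only about 75% of the time. Adding baseline weight to the candidates is therefore not enough.

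**The screen applied to change, by simulation.** N = 74 and a true difference of 4 kg. The protocol gives neither the number of lipid and blood-pressure terms nor any covariate correlations, so these are assumptions:
- BMI (correlation 0.8 with weight) plus 10 covariates unrelated to weight: about 74%
- BMI plus 6 unrelated covariates: about 76%
- BMI as the only candidate (correlation 0.8 to 0.9): 78% to 79%

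The comparator is about 79% for the model that always includes baseline weight. Under no effect, the screened analysis rejects about 5% of the time, so type I error is not the problem.

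**The case against.** The strongest reply is that the declared outcome is weight change and that a change score already uses the 0.9 correlation. Leaving baseline weight out then costs 2 power points, or 2 participants per group. By noncentral t the baseline-adjusted analysis itself falls just short of 80%. This stands, and it sets the size of the point.

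A reader might go further and infer that power collapses, since section 2.8.1 speaks of group differences in body weight. If that meant 6-month weight not adjusted for baseline weight, power would be about 23% unadjusted. With the screen it would be about 40% at an assumed BMI-weight correlation of 0.8, or about 52% at 0.9. The loose wording permits this reading, but the abstract and sections 2.3 and 2.7.1 all say change, so the protocol does not support it.

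Two other inferences also go too far. The baseline similarity check is not stated to decide adjustment; the relation to the outcome does that. Nor does the article plan to adjust for post-treatment values. HbA1c is re-measured at 1 and 6 months (section 2.7.2) and BMI is measured on the same device as weight, but nothing says that lipids or blood pressure are repeated. Baseline values are the natural reading, and a few words would settle it.

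Finally, the regression comes after a group comparison and might be only supportive. That is possible. The text does not say which result is primary, and neither route, as written, conditions on baseline weight.

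**Conclusion.** The point holds in a limited form. The figure of 37 per group is the one for an analysis adjusted for baseline weight, while section 2.8.1 omits baseline weight and selects covariates from the outcome data. The analysis model is thus neither fixed in advance nor the sample-size model.

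For weight change, the loss is about 2 power points without the screen. With it, power is about 74 to 78% against about 79%. The first figure follows from the protocol's own inputs and an equal SD at both times. The second rests on assumed numbers and correlations of covariates. The sample size of 74 need not change on this account if the model is corrected, before any allowance for dropout. This is a should-fix point: the power loss is small, but it bears on the primary result and is easy to repair.

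**What to change.** In section 2.8.1, pre-specify the primary analysis as a linear regression of 6-month weight (or of change; the estimated group effect is the same once baseline weight is in the model) on group, with baseline weight always included. Center and other baseline covariates are optional, but should be fixed in advance and kept whatever their p-values. Drop the p<0.2 screen for the primary analysis and state that all covariates are baseline values. In section 2.3, state that 37 per group assumes this model.

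The cost is a rewritten paragraph before outcomes are analysed and one or a few degrees of freedom. Baseline weight is already collected.

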## 2. Materials and Methods

### 2.1. Study Design and Settings

The study is a single-blind, multicenter randomized parallel-comparison trial with two intervention groups in a 1:1 ratio. Participants were blinded to the allocated group, but researchers performing the intervention were not.

The trial registration code is 10.17605/OSF.IO/4D8FJ and was designed so that it can be reported according to the SPIRIT 2013 statement [30]. The study will be carried out across three centers of the University of Extremadura (UEx).

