#### 2.8.3. Criteria for Discontinuation of Participation in the Study or of the Study

If a participant withdraws consent for participation in the study.If their physician determines that the continuation of the intervention is not preferable for an individual patient. At the moment, there is no reason that can be used to exclude a patient from the trial apart from the aforementioned exclusion criteria, which might minimize bias affecting the results of the study.If the study protocol cannot be followed.

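### Linear regression, the only model named for body weight, makes no use of the 1-month weight; on complete cases its 6-month estimate could be biased if loss follows early response differently by arm

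*Protocol article*

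**What the plan says.** Section 2.7.1 of the protocol article defines the primary outcome over two follow-up visits: "The primary outcome will be identifying changes in body weight from baseline to 1 and 6 months and between groups". Section 2.3 powers the trial on the later visit only, for "80% power to detect a 4 kg difference in mean weight change between groups at 6 months".

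Section 2.8.1 says that group differences in body weight will be examined, without attaching a model. It then screens covariates by their bivariate relation to outcome and names one model: "Adjustment for confounding factors will be examined using linear regression". The candidates are age, sex, center, BMI, HbA1c, lipids and blood pressure. The 1-month weight is not among them, and baseline weight enters only through BMI. No repeated-measures or mixed model appears, and nothing is said about missing weights.

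On follow-up, section 2.8.3 lists reasons for discontinuation, among them consent withdrawal, a physician's decision and "If the study protocol cannot be followed". Section 2.6 expects the live sessions of arm B to help keep participants in follow-up. No dropout rate is given.

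**The concern.** An ordinary regression of 6-month weight has one outcome per person. Someone weighed at baseline and 1 month and then lost adds nothing to it unless the missing weight is imputed. That discards information the trial has already collected, and which bears on both later weight and the chance of staying. Section 2.6 itself treats the first month as decisive for weight loss.

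The arms differ enough for loss to follow different patterns. Arm B has six two-hour sessions in a month, diaries, wristbands, posting tasks and a personal trainer. Arm A has online material and appointment reminders, and no motivation from the researchers. If poor early responders leave one arm more than the other, those who remain are no longer comparable. The 6-month difference is then biased, and the test can reject a true null more than 5% of the time.

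**Working it through.** **1. The plan's own figure.** Section 2.3 gives "14 kg SD in baseline weight and a 0.9 correlation between baseline and 6-month weight", a 4 kg difference, 80% power and two-sided 5%. Section 2.1 gives "two intervention groups in a 1:1 ratio".

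- Baseline-adjusted residual SD = 14 × √(1 − 0.9²) = 6.10 kg.
- n per arm = 2 × (1.960 + 0.842)² × 6.10² / 4² = 36.5, so 37 per arm and 74 in total. This matches "a sample size of 74 (37 per group) was required".
- A change-score analysis has SD = 14 × √(2 × (1 − 0.9)) = 6.26 kg and needs 39 per arm, 78 in total.

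The stated size therefore corresponds to a baseline-adjusted 6-month comparison with 37 complete 6-month weights per arm.

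**2. How much the 1-month weight says about the missing 6-month weight.** The documents give only the 0.9 correlation. Assume 0.97 between baseline and 1 month, and 0.93 between 1 and 6 months. The partial correlation of 1- and 6-month weight given baseline is

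(0.93 − 0.97 × 0.90) / √[(1 − 0.97²)(1 − 0.90²)] = 0.057 / 0.106 = 0.54.

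With 0.95 in place of 0.97 it is 0.075 / 0.136 = 0.55. The 1-month weight thus explains about 0.54² = 29% of the variance left after baseline: enough to bias complete cases, but not enough to recover much power.

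**3. Bias under loss that depends on early response.** Weights at the three visits were simulated as jointly normal with SD 14 kg and a true 6-month effect of 4 kg in favour of arm B. The log-odds of loss after 1 month rise with 1-month weight gain.

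*Large sample:* 300,000 per arm; baseline to 1-month correlation 0.95–0.97; 1-month effect 1–2 kg; 20–30% loss overall; log-odds slope 0.15–0.3 per kg where loss is the same in both arms and 0.3 per kg elsewhere. Entries are estimates in kg.

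| Loss depends on early response | Complete-case 6-month ANCOVA | Analysis using 1-month weight |
|---|---|---|
| Equally in both arms | 3.7 to 4.0 | 4.0 |
| In arm B only | 4.5 to 5.0 | 4.0 |
| In opposite directions in the two arms | 5.1 to 6.1 | 4.0 |

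The last column is within 0.05 kg of the truth in every scenario.

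*Trial size:* 37 per arm, correlations 0.97 and 0.93.

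- Dependence in arm B only: the complete-case estimate is 4.7–5.1 kg and a true null is rejected 7–10% of the time. For example, 15% random loss in A and about 25% in B, with slopes of 0.3–0.5 per kg, gives 4.7–5.0 kg and 7.7–9.0%.
- The same dependence in both arms: 3.6–3.7 kg and about 5% rejection.
- The analysis using 1-month weight gives 4.0 kg throughout.

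**4. Power under purely random loss.** With 20% loss, 37 × 0.8 = 29.6 per arm remain, and the normal approximation gives 71%. Using the 1-month weight, the variance is inflated by 0.71 / 0.8 + 0.29 = 1.18 instead of 1 / 0.8 = 1.25. The effective size is 37 / 1.18 = 31.4 per arm, close to the 15% loss case, for which power is 74%. Simulation at trial size, which uses t rather than normal tests, gives 68% against 70%. The gain is about 2 points.

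**The case against.** The strongest objection is that much of this is silence in a condensed article whose analysis plan is not shown. A reader might infer that the regression will be run separately at each visit and that anyone without a 6-month weight will be dropped. Section 2.8.1 says neither. Its sentence on regression concerns adjustment for confounding, and imputing missing weights first, even from the 1-month weight, would be compatible with the text. This stands: missing-data handling may properly sit in the analysis plan, and its absence here is not the point.

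A reader might also infer that loss will be heavier in arm B and will flatter it. The documents do not support that. Arm B is more demanding, but it also has live sessions meant to aid retention, a trainer and steady feedback, so heavier loss in arm A is at least as plausible. The item "If the study protocol cannot be followed" stands under a heading that covers both a participant and the whole study; it does not say which, nor that someone who stops the sessions will not be weighed. If loss depends on early response equally in both arms, the bias is small and towards the null.

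Finally, linear regression is consistent with the sample-size calculation, and the power gain from changing it is slight. Both are true. What remains is that the article does name a method, and that method, with its listed covariates, does not use one of the two follow-up weights in its own primary outcome. A better one is available from the same data.

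**Conclusion.** The concern holds in a conditional form. As named, the model and covariates leave the 1-month weight out of the 6-month comparison. If the regression is also run without imputation, its estimate of a true 4 kg effect would be about 3.6–4.0 kg when loss depends on early response equally in both arms. It would be about 4.5–5.1 kg, with roughly 7–10% false positives, when that dependence is confined to arm B. Opposite patterns in the two arms would push it further, to 5.1–6.1 kg.

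These ranges rest on assumed correlations, an assumed 1-month effect, assumed loss of about 15–30% and an assumed strength of dependence. Only the SD, the 0.9 correlation, the 4 kg effect and the arm size come from the protocol. Neither the presence nor the direction of such bias can be read from the documents. The case for change is protection against bias, not power. It should be made before the analysis, but it does not undermine the design.

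**What to change.** Make the primary analysis of the 6-month between-group difference a mixed model for repeated measures on the 1- and 6-month weights. Include arm, visit, arm × visit, baseline weight × visit and center, with unstructured covariance, and every participant who has at least one post-baseline weight. Linear regression of 6-month weight after multiple imputation that includes the 1-month weight is an acceptable equivalent. In either case add a sensitivity analysis for data missing not at random, for example by shifting the unobserved 6-month weights by stated amounts in each arm.

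The cost is slightly more analysis work. No extra visits or data are needed, and the SPSS package already named has a mixed-model procedure. The analysis relies on weights being missing at random given the observed ones. That is an assumption, but a weaker one than a complete-case regression without the 1-month weight needs.

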#### 2.7.2. Secondary Outcomes

All secondary outcomes will be assessed at baseline, 1 and 6 months after the intervention.

A secondary outcome will be accomplishing regular physical activity (>30 min/day or >4 h/week). To assess physical activity, participants will complete the RAPA questionnaire. This questionnaire in the Spanish version obtained good test–retest reliability (r = 0.906), a sensitivity of 76.6% and a specificity of 65.6% [36].

Another secondary outcome will be decreasing sugary food intake or avoiding it altogether and increasing vegetable/fruit intake. We will use the Tfeq-Sp, Yale food addiction and EEQ to assess current diet and willingness to change it. The Tfeq-Sp measures three concepts: cognitive restraint, emotional eating, and uncontrolled eating. These concepts are explained further in Jauregui-Lobera et al. [37]. The internal consistency of the Tfeq-Sp was determined by means of Cronbach’s α coefficient, with values ranging between 0.75 and 0.87 [37]. The Yale food addiction questionnaire identifies individuals with addictive behaviors toward food in accordance with substance dependence criteria. The validated Spanish version demonstrated internal consistency for the one single dimension solution of α = 0.95 [38]. The EEQ measures three factors: disinhibition, high-calorie food preference, and feelings of guilt. EEQ internal consistency was good (α = 0.753) [39].

Lowering HbA1c levels to non-diabetic status, when necessary, will also be a secondary outcome. To measure HbA1c, we will employ the Affinity A1c Analyzer.

Finally, changes in diabetes knowledge will be measured using the DKQ-24 questionnaire. This questionnaire was designed to assess overall diabetes knowledge according to content recommendations in the National Standards for Diabetes Patient Education Programs. The 24-item version of the DKQ-24 attained a reliability coefficient of 0.78, indicating internal consistency [40].

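### The questionnaire analysis is framed as change between visits, and the named covariates omit the baseline score; adjusting for it would gain precision at no cost

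*Protocol article*

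**What the plan says.** Section 2.8.1 gives the questionnaires one sentence: "Questionnaire scores will be assessed, and changes will be sought between baseline, 1 and 6 months and between groups". Section 2.7.2 uses the same language for knowledge: "Finally, changes in diabetes knowledge will be measured using the DKQ-24 questionnaire".

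On adjustment, section 2.8.1 says "Covariates will be screened in bivariate analyses and included in multivariable analysis when related to outcomes", with a threshold of p < 0.2. It then names the candidates: "Covariates will include age, sex, center, BMI, HbA1c, lipid profile and blood pressure". The model is given in general terms: "Adjustment for confounding factors will be examined using linear regression". No baseline questionnaire score is named.

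The baseline scores will exist, because section 2.7.2 states: "All secondary outcomes will be assessed at baseline, 1 and 6 months after the intervention". The instruments are RAPA (activity), Tfeq-Sp, Yale food addiction and EEQ (eating behaviour), and DKQ-24 (knowledge). Activity differs from the rest because its outcome is defined as attaining a level: "A secondary outcome will be accomplishing regular physical activity (>30 min/day or >4 h/week".

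**The concern.** A score's own baseline value is usually the best single predictor of its follow-up value. The section makes change the target and lists covariates that leave this predictor out. Analysts working from that text would most naturally compare mean changes, or fit a repeated-measures model and read off the group-by-time term. Either way they subtract the whole baseline value instead of the part that predicts follow-up.

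This has two consequences. The between-group contrast has a larger variance than it needs. It also over-corrects for chance differences at the start: an arm that happens to begin lower on a score appears to improve more, through regression to the mean. With 37 per arm, small chance imbalances are ordinary. These scores carry the trial's evidence on eating behaviour and knowledge and, through RAPA, on activity.

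**Working it through.** **The plan's own figure.** The only sample size calculation is for body weight (section 2.3): SD 14 kg, correlation 0.9, difference 4 kg, two-sided 5%, 80% power, 37 per group. The formula is n = 2(1.96 + 0.8416)² × variance / 4², with (1.96 + 0.8416)² = 7.849.

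- Baseline-adjusted: variance 14² × (1 − 0.9²) = 37.24 (SD 6.10 kg). n = 2 × 7.849 × 37.24 / 16 = 36.5, so 37 per group and 74 in total. This matches the protocol.
- Change score: variance 14² × 2(1 − 0.9) = 39.2 (SD 6.26 kg). n = 2 × 7.849 × 39.2 / 16 = 38.5, so 39 per group and 78 in total.

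The stated 74 is therefore reached with baseline adjustment. This concerns weight only. No calculation is given for any questionnaire.

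**What the questionnaire sentence leads to.** Three analyses fit its wording.

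1. A change-score test compares mean changes.
2. A repeated-measures model with baseline as a time point and unconstrained baseline means has, with complete data, a group-by-time contrast from baseline to a given visit that equals the difference in mean change. Its variance and its sensitivity to imbalance are those of option 1.
3. A regression that includes the baseline score avoids the loss. The text does not name it.

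**Size of the loss under options 1 and 2.** Inputs: 37 per arm (section 2.3); equal SD at both visits, set to 1 (assumption); r between baseline and follow-up score (assumption, range 0.3 to 0.9).

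- Variance of a change score: 2(1 − r). Variance after baseline adjustment: 1 − r².
- Ratio, adjusted to change: (1 − r²) / [2(1 − r)] = (1 + r)/2. Saving: 1 − (1 + r)/2 = (1 − r)/2.
- One standard error of baseline imbalance: √(2/37) = 0.23 SD. Shift in the change contrast: (1 − r) × √(2/37).
- Power: noncentral t, 37 per arm, two-sided 5%, for a difference of 0.5 SD (assumed for illustration).

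| Assumed r | Ratio (1 + r)/2 | Variance saving | Power, change | Power, adjusted | Shift from 1-SE imbalance |
|---|---|---|---|---|---|
| 0.3 | 0.65 | 35% | 43% | 60% | 0.16 SD |
| 0.5 | 0.75 | 25% | 56% | 69% | 0.12 SD |
| 0.7 | 0.85 | 15% | 78% | 84% | 0.07 SD |
| 0.9 | 0.95 | 5% | – | – | 0.02 SD |

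In the same units, a comparison of follow-up scores that ignores baseline has variance 1. The change score has 1.4 at r = 0.3 and 1.0 at r = 0.5, so below 0.5 it is worse than not using baseline at all.

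**Can the document narrow r?** The one questionnaire correlation it reports is for RAPA: "This questionnaire in the Spanish version obtained good test–retest reliability (r = 0.906), a sensitivity of 76.6% and a specificity of 65.6". That is a test-retest reliability, not a correlation between baseline and 6 months under an intervention, so it fixes r neither high nor low.

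**The case against.** The strongest objection is that the quoted sentence names no dependent variable, test or model. The article is condensed, and the model for secondary scores is commonly left to a fuller plan that is not shown. The covariate wording need not be exhaustive, and not naming a baseline score is not the same as excluding it. The protocol also uses change loosely: section 2.3 speaks of a difference in mean weight change, yet its 37 per group matches a baseline-adjusted analysis.

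Most of this stands, and it rules out the stronger reading that a reader might infer: that the plan prescribes raw change scores, fixes a closed covariate list and bars the baseline score from every model. The document says none of these things. Nor does it support a claim that r is well below 0.9 for these scores.

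It is also fair that the variance formulas do not apply to activity as a threshold outcome. The same caution applies to the Yale instrument if it is used to classify people and not as a score.

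What survives is narrower. The text does state a target, which is change, and it does name adjustment variables, which omit the baseline score. Of the three analyses that fit the wording, two lose precision, and nothing in the section points to the third.

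**Conclusion.** The point holds as an improvement to the analysis of secondary outcomes. Followed as written, through change scores or a group-by-time contrast, the questionnaire comparison remains unbiased over randomisation. A reader might infer a biased treatment effect; that does not follow. The cost is precision, together with a partial carry-over of whatever baseline imbalance chance produces.

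The variance saving from adjustment is (1 − r)/2: 35%, 25%, 15% or 5% at r = 0.3, 0.5, 0.7 or 0.9. It is worthwhile at moderate correlation and negligible at 0.9. The figures rest on an assumed r, equal variances at both visits, complete data and, for the power column, an assumed difference of 0.5 SD. They apply to the continuous scores and not to the activity threshold. The body-weight analysis is a separate matter and is not judged here.

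**What to change.** Replace the questionnaire sentence in section 2.8.1 with wording such as:

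*For each continuous questionnaire score (Tfeq-Sp scales, EEQ, DKQ-24, and Yale food addiction if scored continuously), groups will be compared at 1 month and at 6 months by linear regression of the follow-up score on group and the baseline value of the same score. The baseline value is always included and is not subject to the p < 0.2 screen. The adjusted between-group difference will be reported with its 95% confidence interval. Regular physical activity, defined as reaching the stated threshold, will be compared with a binary model that includes group and the baseline RAPA value. Changes within each group are descriptive.*

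The two time points keep the standing that section 2.7.2 gives them, with neither ranked above the other. If the team prefers to report change, regressing the change score on group and baseline gives the same group difference, so the language of change can stay.

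The cost is a few lines of text. No new data, visits or participants are needed, because the baseline scores are already collected. If a fuller analysis plan already specifies this, it is enough to confirm it.
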